**Fig. 2 Fig2:**
[figure not shown]
Kaplan–Meier curve comparing overall survival between patients with routine follow-up imaging and symptomatic follow-up in the Netherlands between 2014–2019 (unpublished data)

As we expect 80% of patients to accept the experimental intervention offered in the intervention arm of the study, an estimated refusal rate of 20% needs to be taken into account. This leads to a decrease of the overall survival to 29.4 months (80% × 32.0 months + 20% × 19.0 months) for patients in the intervention arm. Moreover, despite that current non-standardized follow-up in daily clinical practice mainly results in a symptomatic follow-up approach without routine imaging, data from our recurrence database showed that 85/1580 patients (5%) did nonetheless receive routine follow-up imaging based on shared-decision making (the remaining 199/284 patients (70%) who received routine follow-up imaging participated in a clinical study with a study-specific follow-up including routine imaging). This results in a slight increase of the suspected overall survival in the control arm to 19.7 months (95% × 19.0 months + 5% × 32.0 months). The clinically relevant survival difference of 29.4 months vs. 19.7 months for the intervention and control arm, respectively, also approximates the mean survival difference of 9.5 months presented in the meta-analysis from Halle-Smith et al. [33]. These numbers correspond to a relative hazard (RH) of survival of 1.49, which is used to calculate the sample size of the study. Furthermore, as we expect a minimal level of loss to follow-up in this surveillance study, a censoring rate of 1% is expected each month.

To detect a 49% overall survival improvement (RH of survival 1.49) for patients in the intervention group, as compared with the control group, with a statistical power of 80% and a 0.05 two-sided significance level, a sample size of 306 patients is required. This calculation was based on the assumption of an exponential model, a median overall survival of 19.7 months in the control arm, a follow-up duration of 30 months, a drop-out rate of 1% and a baseline event rate of 3.5%. Following this calculation, we plan to include 306 patients in total: 153 patients in the recurrence-focused follow-up group and 153 patients in the non-standardized, symptomatic follow-up group.

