### Assignment of interventions: allocation

#### Sequence generation {16a}

The allocation sequence to randomly assign participants into groups is based on computer-generated random numbers, following 2–4-6 variable block randomization, with stratification for institute. Eligible patients are randomized in chronological order.

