### Statistical methods

#### Statistical methods for primary and secondary outcomes {20a}

The latest version of R Studio will be used for statistical analysis.

Baseline characteristics will be reported using standard descriptive statistics. Success of randomization will be evaluated by eye-balling whether the distribution of baseline characteristics between the intervention and control group is even. Primary analysis will be performed according to the intention-to-treat principle. As such, patients randomized to the intervention arm of the trial who refuse recurrence-focused surveillance following the TwiCs design will be analyzed as part of the intervention group. The main study parameter is overall survival, measured as the time from the date of PDAC resection to the date of death. Patients are censored at the time of last known follow-up visit documented if no event occurred. Overall survival rates will be reported as median with 95% CI and will be calculated by the Kaplan–Meier survival curve method. Log-rank test will be used to compare survival between the intervention and control group. One- and 2-year survival probabilities will be calculated. Univariate Cox-proportional hazard analysis will be used to assess the crude effect of a recurrence-focused surveillance strategy on survival. In addition, adjusted effect estimates will be calculated using a multivariable Cox-proportional hazard model, including potential confounders for symptomatic PDAC recurrence. To address potential confounders for which the multivariable analysis needs to be adjusted, a Directed Acyclic Graph was designed on https://www.dagitty.net (Fig. 3). It is hypothesized that a recurrence-focused postoperative surveillance strategy leads to the detection of PDAC recurrence in an asymptomatic stage, which increases the probability to undergo treatment for recurrence, possibly improving survival. The association between postoperative surveillance strategy and overall survival is therefore fully mediated through presence of symptoms at the time of recurrence diagnosis and subsequent administration of recurrence treatment. Given that the median overall survival after resection of PDAC is 21 months and 1- and 2-year survival rates are 75% and < 50%, respectively, we expect that during our follow-up period at least 50% of included patients (*n* = 153) will experience an event. The number of variables included in the multivariable analysis is based on the rule of thumb of ~ 10 events per variable, where a categorical variable counts for the number of categories. Consequently, multivariable analysis is adjusted for 15 baseline covariates that are considered to be the most important, i.e., age (continuous), sex (male/female), and predictors that reflect an (un)favorable tumor biology or treatment course, including performance status (continuous), preoperative CA 19–9 value (continuous), tumor location (head/distal), resection margin status (R0/R1), tumor size (continuous), number of positive lymph nodes (continuous) and tumor differentiation (poor/well-moderate), and administration of adjuvant therapy (yes/no). Given that recurrence treatment is considered a mediator, and not a confounder, no adjustment for recurrence treatment is required. Because administration of neoadjuvant therapy is known to affect preoperative CA 19–9 values, resection margin status, tumor size, and number of positive lymph nodes, neoadjuvant treatment will not be adjusted for. Postoperative complications are deemed to affect the receipt of adjuvant therapy and will thus not be included in multivariable analysis. Results will be presented as hazard ratio’s (HR) with corresponding 95% confidence intervals (CI). A two-tailed *P-*value < 0.05 will be considered statistically significant.

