### Trial status

Protocol version 4.0, October 24, 2023. The first patient was enrolled on March 16, 2021. At the time of submission of this manuscript (January 2, 2024), 219 patients have been enrolled by 7 institutions. Recruitment is anticipated to be completed in April 2024.

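### Randomisation is stratified by institute but every overall survival analysis described leaves institute out; the test stays valid, but loses power if prognosis differs between institutes

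*Protocol article*

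**What the plan says.** Protocol article, Sequence generation {16a}: allocation is computer-generated, "following 2–4-6 variable block randomization, with stratification for institute".

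Statistical methods for primary and secondary outcomes {20a} describes three analyses of overall survival:

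- The primary comparison: "Log-rank test will be used to compare survival between the intervention and control group".
- The unadjusted estimate: "Univariate Cox-proportional hazard analysis will be used to assess the crude effect of a recurrence-focused surveillance strategy on survival".
- The adjusted estimate: "multivariable analysis is adjusted for 15 baseline covariates that are considered to be the most important, i.e., age (continuous), sex (male/female"), followed by performance status, preoperative CA 19-9, tumour location, margin status, tumour size, positive nodes, differentiation and adjuvant therapy.

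Institute appears in none of them. The other stratified analyses in {20a} and {20b} concern recurrence pattern, type of treatment and receipt of recurrence treatment.

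Trial status reports that "219 patients have been enrolled by 7 institutions" when the article was submitted.

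**The concern.** Blocking within institute forces the arms to be balanced inside each centre, so differences in prognosis between centres are largely removed from the treatment contrast. An analysis that ignores institute does not use that balance. If centres differ in prognosis, its standard error is too large for the design, and the crude hazard ratio, which averages over centres, is pulled towards 1. The result is a test that rejects less often than its nominal 5% under the null and has less power under the alternative. At stake is some of the power for overall survival, which could be kept by analysing within the groups already used for randomisation.

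**Working it through.** **1. Is institute really left out?** {20a} allows about 10 events per variable, expects at least 153 events, and counts a categorical variable by its number of categories. 153 / 10 is about 15.

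- Continuous, one each: age, performance status, CA 19-9, tumour size, positive nodes = 5.
- Binary, two each: sex, tumour location, margin status, differentiation, adjuvant therapy = 5 × 2 = 10.
- Total: 5 + 10 = 15, exactly the stated number.

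The list is full without institute.

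**2. Reproducing the plan's sample size.** Inputs from Sample size {14}: relative hazard 1.49, two-sided 0.05, 80% power, monthly event rate 3.5%, 1% monthly censoring, 30 months.

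- Events (Schoenfeld): 4 × (1.960 + 0.842)² / (ln 1.49)² = 197.4, so 198.
- Event probability in an arm with rate l and censoring rate c: l/(l + c) × (1 − exp(−30(l + c))). With l = 0.035 this is 0.576; with l = 0.035 × 1.49 it is 0.709; the mean is 0.643.
- N = 197.4 / 0.643 = 307, or 308 when rounded up to equal arms, against the stated 306.

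This match multiplies the baseline rate by 1.49. With the intervention rate at 0.035 / 1.49, the direction of benefit, the mean event probability is 0.510. Then 306 patients give about 156 events and about 70% power. That is a separate matter; it is noted only because it explains why power below starts near 70%.

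**3. Effect of ignoring institute.** The two statistics are

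- unstratified: z = U/√V, with U = Σ(aⱼ − pⱼ) and V = Σpⱼ(1 − pⱼ) over all deaths, where aⱼ marks an intervention-arm death and pⱼ is that arm's share of those at risk;
- stratified: z = ΣUₖ/√ΣVₖ, with the same sums taken within each institute k.

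Simulated trials: 306 patients, 1:1, blocks of 2, 4 and 6 within institutes of unequal size, control hazard ln 2 / 19.7, hazard ratio 1 or 1/1.49, 1% monthly loss, 30 months, 4,000 to 6,000 runs per setting. Assumptions not in the documents: normal institute effects on the log hazard with the SD shown, and 16 as an alternative number of institutes. SDs of 0.3, 0.5 and 0.8 mean hazards differing by factors of exp(0.3) = 1.35, exp(0.5) = 1.65 and exp(0.8) = 2.23 per SD.

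| Institutes | SD | Type I error, unstratified | Power, unstratified | Power, stratified |
|---|---|---|---|---|
| 7 | 0 | 5.1% | 70.6% | 69.8% |
| 7 | 0.1 | 5.1% | 70.2% | 69.8% |
| 7 | 0.2 | 4.9% | 69.0% | 69.3% |
| 7 | 0.3 (two runs) | 4.8%, 5.4% | 68.8%, 68.4% | 70.1%, 69.4% |
| 7 | 0.5 | 3.9% | 65.0% | 70.6% |
| 7 | 0.8 | 3.0% | 56.2% | 68.7% |
| 16 | 0 | 5.4% | 70.4% | 68.2% |
| 16 | 0.3 | 4.6% | 67.7% | 67.8% |
| 16 | 0.5 | 3.5% | 64.8% | 67.5% |
| 16 | 0.8 | 2.4% | 55.6% | 68.6% |

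Monte Carlo standard error with 4,000 runs: √(0.05 × 0.95 / 4,000) = 0.3 points for type I error and √(0.7 × 0.3 / 4,000) = 0.7 points for power. The stratified test's type I error was 4.6% to 5.6%, apart from 6.1% in one of the two runs at SD 0.3 (4.9% in the other).

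**4. Repeat checks, 7 institutes.** A separate simulation gave unstratified type I error of 5.0%, 4.6% and 3.9% at SDs of 0, 0.3 and 0.5. Unstratified versus stratified power was 70.1% vs 69.2%, 68.3% vs 69.6% and 64.8% vs 69.6%. Letting follow-up run from 30 to 58 months (28 months of accrual), SD 0.3 gave unstratified type I error of 4.4% and power of 74.3% vs 75.0%.

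**The case against.** A reader might infer that the primary test's true error rate is below 5% and that power is certainly being given away. The documents do not support that. They report nothing on survival differences between institutes, and with an SD up to 0.3 the unstratified test is close to nominal. With no institute effect it is slightly the more powerful of the two. Non-standardised follow-up in two countries does not fill the gap. It describes control-arm care rather than baseline prognosis, and Trial status does not say how many of the 7 institutions are in the UK.

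A second objection is that the analysis plan is not shown and may stratify the test. That would carry weight if the article had been silent. But it names the test, calls one Cox model univariate, and closes the covariate list at a count that leaves no room for institute. A plan that stratifies would have to depart from this text.

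A third objection is that stratifying is not free. This stands in part. Seven institutes is a snapshot at 219 of 306 patients, and Recruitment {15} expects all Dutch pancreatic centres to take part. With 16 unpooled strata and no institute effect, the stratified test loses about 2 points, so a pooling rule is a necessary part of the change.

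**Conclusion.** The mismatch between design and analysis is in the text and can be stated with high confidence. Its consequence is conditional. With 7 institutes, ignoring institute costs at most about 1 point of power up to an assumed SD of 0.3, with type I error near 5%. At SD 0.5 it costs about 5 points, with type I error about 3.9%. Only at SD 0.8, where hazards differ more than twofold per SD, does the loss reach about 12 points. The trial's validity is not in question, because any error is conservative. The change is worth making because it is cheap and protects against a loss that cannot be ruled out, not because a loss has been shown.

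**What to change.** Before outcomes by arm are examined, state that the primary log-rank test is stratified by institute, and that the crude and adjusted Cox models use institute as a stratum. Add a rule that pools institutes with few patients within country, based on enrolment counts only and fixed in advance. If the sponsor prefers to leave institute out, give the reason. Fixing this now avoids a choice between two tests after the results are known.

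The cost is a short amendment and no new data. A stratified Cox model estimates no institute coefficients, so the count of 15 under the events-per-variable rule is unchanged. The resulting hazard ratio is a within-institute effect and should be reported as such. If institutes turn out not to differ, the price is about 1 point of power with 7 strata, or about 2 points with 16 strata left unpooled.

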### Who will take informed consent? {26a}

The inclusion and randomization process of the RADAR-PANC trial is schematically shown in Fig. 1. Potentially eligible subjects are identified by the (local) investigator or an authorized delegate, by checking pathology reports of patients with known or suspected PDAC after intended radical resection. The (local) investigator or an authorized delegate will confirm that a potentially eligible patient is included in the PACAP or PACOPS cohort and signed informed consent for being randomized in future studies according to the TwiCs design and participation in quality of life questionnaires. If not, the patient will continue standard of care and will not be randomized for this trial. If the patient meets all the eligibility criteria for the RADAR-PANC trial, the participant is randomized for postoperative surveillance strategy with a 1:1 allocation ratio. Participants are either randomized for follow-up according to the current, non-standardized practice (control), or recurrence-focused surveillance according to the trial protocol (intervention). If the patient is randomized to the control arm, no additional action is taken: patients will receive current standard of care and are not explicitly informed about being randomized to the control arm of the trial according to the TwiCs design. Patients randomized to the intervention arm of the trial will be approached by a researcher and will be offered the experimental intervention within the first 3 to 4 months post-surgery. These patients are informed that they are free to decide whether they want to accept or deny the intervention. Oral and written information is provided and the treating physician is informed. If the patient chooses to participate, the additional informed consent form is signed prior to the start of the intervention.

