### Intervention description {11a}

The intervention exists of a recurrence-focused follow-up approach with routine imaging and serial serum tumor marker testing. The follow-up scheme of the RADAR-PANC trial is based on current surveillance guidelines after resection for PDAC as recommended by the National Comprehensive Cancer Network (NCCN) [11]. This intense follow-up scheme was chosen to increase the chance of early diagnosis of disease recurrence. For the first 2 years after surgery, clinical evaluation, serum carbohydrate antigen 19–9 (CA 19–9) testing, and contrast-enhanced CT imaging of chest and abdomen is performed every 3 months.

Follow-up of patients and related procedures (i.e., blood draws, CT scans) in this study can be performed at the participating hospital, referring hospital, or central coordinating hospital. Study-related follow-up is performed at 3, 6, 9, 12, 15, 18, 21, and 24 months after surgery. For the first follow-up evaluation, patients need to be randomized within the first 3 to 4 months post-surgery. Follow-up appointments are made by the trial coordinator in consultation with the treating clinician. If possible, outpatient clinic visits are combined with CT scan appointments; blood samples are obtained simultaneously.

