#### CT imaging

During the first 2 years of follow-up, a CT of chest and abdomen with intravenous contrast (late arterial phase of the upper abdomen and portal venous phase covering the entire abdomen) is performed at 3 months postoperatively and every subsequent 3 months.

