### Recruitment {15}

To achieve adequate patient enrolment and reach the target sample size, all centers are encouraged to participate in the current trial. To ensure enrolment of all eligible patients, the study coordinator(s) are in close contact with the local investigators at the participating centers to obtain weekly updates about patients who underwent macroscopically radical PDAC resection. Eligible patients will be contacted by the study coordinators in consultation with the treating clinicians. If an eligible patient is not yet approached for participation in the PACAP or PACOPS project, informed consent for PACAP or PACOPS, including TwiCs and PROMs, will be discussed by the study coordinator(s).

In 2018, 2348 patients were diagnosed with pancreatic cancer in the Netherlands. About 20% (*n* = 470) of these patients underwent macroscopically radical (R0-R1) resection of the tumor. In the Netherlands, all pancreatic resections are performed in centers affiliated with the DPCG, which will all participate in the current study. Based on the current successful enrolment progress, we anticipate that 75% (*n* = 353) of all patients will be registered yearly in the PACAP cohort and that 80% (*n* = 282) of these patients will provide informed consent for the TwiCs design. About 150 patients each year are expected to be included in other studies with a study-specific follow-up, which is an exclusion criterium for the RADAR-PANC trial. This leaves 282 – 150 = 132 patients eligible for randomization in the current study each year. Fifty percent (*n* = 66) of patients will be randomized to a standardized surveillance strategy. We expect that 80% (*n* = 53) of these patients are willing to participate in the intervention arm of the study, with a participation rate of 100% (*n* = 66) in the control arm as a consequence of the TwiCs design. The expected time needed for inclusion of a total of 306 patients (153 patients in each arm) is therefore 28 months. The final analysis will be performed 30 months after the last patient is enrolled.

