
Data on the incidence of PDAC recurrence, compliance to a recurrence-focused surveillance strategy, clinical, and radiological patterns of recurrence, eligibility for treatment of recurrence, administration of recurrence treatment, as well as type of treatment, reasons to refrain from recurrence treatment, and patient tolerance to recurrence treatment (i.e., completion of treatment as planned) will be analyzed and reported using descriptive statistics. Chi-square or Fisher’s exact test are used to compare categorical variables as appropriate. Parametric continuous variables are presented as mean ± standard deviation (SD) and are compared using the Student’s *t*-test. Non-parametric continuous variables are presented as median with interquartile range (IQR) and are compared using the Mann–Whitney *U* test. Patient-reported outcomes at each time point during follow-up will be compared to baseline scores using a generalized linear mixed model approach to assess a difference in patients’ quality of life and worry of cancer recurrence between the trial arms. Scores will be presented as mean (± SD), changes from baseline as mean differences (MD) and estimates will be calculated to represent a difference in MD between groups with corresponding 95% confidence intervals (CI). Minimally important differences (MIDs) for the EORTC QLQ-C30 will be interpreted based on Musoro et al. for available quality of life domains [34]. If not specified, a ≥ 10-point change is considered meaningful. Disease-free survival and post-recurrence survival will be assessed using Kaplan–Meier survival curves and reported as median with 95% CI. The log-rank test will be used to compare groups. Cox proportional hazards model will be used when appropriate. Stratified analyses will be performed regarding pattern of disease recurrence and type of additional treatment. Various baseline parameters (e.g., sex, age, body mass index (BMI), Charlson Comorbidity Index (CCI), ECOG score, postoperative complications, (neo)adjuvant therapy, resectability status, preoperative CA 19–9 values, tumor location, resection margin status, vascular resection, tumor (T) stage, lymph node (N) stage, tumor differentiation, perineural growth) will be collected. The yield of CT surveillance and role of serum tumor marker testing is assessed by calculating diagnostic accuracy values, i.e., sensitivity, specificity, false-positive and false-negative values. Cost-effectiveness is calculated using a Markov model.

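### Receipt of adjuvant therapy is treated as a baseline covariate, but nothing fixes its value at randomisation, so the additional adjusted hazard ratio may condition on something that allocation can change

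*Protocol article*

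**What the plan says.** All places are in the protocol article.

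- **Statistical methods {20a}, the model.** The adjusted Cox model is introduced with "multivariable analysis is adjusted for 15 baseline covariates that are considered to be the most important". The list closes with "tumor differentiation (poor/well-moderate), and administration of adjuvant therapy (yes/no". The variable is receipt, not intention, and it has no date limit.
- **Statistical methods {20a}, data collected.** The baseline label recurs: the parameters named as baseline include "ECOG score, postoperative complications, (neo)adjuvant therapy, resectability status".
- **Statistical methods {20a}, reasons for leaving variables out.** Recurrence treatment is not adjusted for because it is a mediator. On complications, the section says: "Postoperative complications are deemed to affect the receipt of adjuvant therapy".
- **Who will take informed consent? {26a}.** Candidates are found "by checking pathology reports of patients with known or suspected PDAC after intended radical resection".
- **Recruitment {15}.** Coordinators contact centres "to obtain weekly updates about patients who underwent macroscopically radical PDAC resection".
- **Intervention description {11a}.** The outer limit is that "patients need to be randomized within the first 3 to 4 months post-surgery".
- **Participant timeline {13}.** Allocation stands in the postoperative column, ahead of the 3-month visit.
- **CT imaging.** In the intervention arm the scan "is performed at 3 months postoperatively and every subsequent 3 months".

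The primary comparison in {20a} is the intention-to-treat log-rank test, followed by a univariate Cox model. The multivariable model is additional to these.

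**The concern.** A covariate adjusted for in a randomised comparison should be fixed before allocation can influence it. Adjuvant therapy is the only treatment in this model that may begin after allocation. By the article's own account its receipt depends on postoperative complications, so it is settled in the same months in which patients are randomised.

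The more specific worry is the label. Take an intervention patient who has not started chemotherapy and whose month-3 CT leads to a diagnosis of recurrence. Later chemotherapy may then be recorded as recurrence treatment, and adjuvant therapy as no. A similar control patient without a routine scan may start the same chemotherapy and be recorded as yes. Patients with a poor prognosis then leave the adjuvant-yes group in one arm only, and the adjusted comparison is no longer like with like. Part of the mediator that {20a} deliberately leaves out would return through this covariate.

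**Working it through.** **1. The plan's covariate count.** Expected events: 306 × 50% = 153. At about 10 events per variable, 153/10 = 15.3. Ten covariates are listed. Five are continuous (age, performance status, CA 19-9, tumour size, positive nodes) and five are binary (sex, location, margin, differentiation, adjuvant therapy). Counting categories as the plan does: 5 × 1 + 5 × 2 = 15. The stated 15 reproduces.

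**2. Is the covariate fixed at randomisation?** Randomisation can follow directly on the pathology report, with weekly case finding, or come as late as 3 to 4 months after surgery. The article gives no start or decision date for adjuvant therapy and does not limit the variable to therapy begun or decided by randomisation. So for some patients the value may be settled after allocation. How many cannot be read from the article.

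**3. Can allocation change it?** The first arm-specific test is the month-3 CT with CA 19-9. No rule says how chemotherapy started after an early recurrence is to be coded. The route is open, but only for patients whose adjuvant status is still open at that scan.

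**4. How large could the bias be?** The article has no figures for this, so the inputs below are assumptions except where marked.

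- 300,000 simulated patients, 1:1.
- Monthly hazard 0.0352 (ln 2/19.7, control median from Sample size {14}); dropout 1% per month (same section); censoring at 44 months.
- Early recurrence in about 13%; about 73% fit for and receiving chemotherapy.
- Log hazard: +0.8 for early recurrence, −0.4 for chemotherapy whatever its label, +0.6 per standard deviation of unmeasured severity.
- Share with adjuvant status open at the first CT: 20%, 50% or 90%.
- Share of those with early recurrence in the intervention arm who are relabelled: 0, 50% or 100%.

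Hazard ratio from a Cox model with arm and the adjuvant label (0 / 50% / 100% relabelled):

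| Status open | True HR 1.00 | True conditional HR 0.671 (1/1.49) |
|---|---|---|
| 20% | 0.998 / 0.995 / 0.992 | 0.715 / 0.712 / 0.709 |
| 50% | 0.998 / 0.990 / 0.981 | 0.715 / 0.708 / 0.700 |
| 90% | 0.998 / 0.983 / 0.964 | 0.715 / 0.702 / 0.686 |

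The crude hazard ratios are 1.000 and 0.721. In the right-hand column the reference is 0.715 rather than 0.671, because the fitted model leaves out severity and early recurrence.

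Shift against no relabelling:

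- True HR 1.00: from 0.995/0.998 = 0.997 to 0.964/0.998 = 0.966, or 0.3% to 3.4%.
- True HR 0.671: from 0.712/0.715 = 0.996 to 0.686/0.715 = 0.959, or 0.4% to 4.1%.

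A separate simulation under no effect (30 replicates of 3,000 patients) assumed 10% early recurrence with a median survival of 9 months, 70% receiving chemotherapy and 80% uptake of surveillance. Unadjusted, arm-dependent-label and arm-independent-label hazard ratios were 1.017, 1.012 and 1.016 with 30% late starters, and 0.993, 0.988 and 0.994 with 50%. The arm-dependent label lowers the estimate by about 0.5% (1.012/1.017 = 0.995; 0.988/0.993 = 0.995).

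**5. Against the trial's precision.** With 153 events and 1:1 allocation, the standard error of the log hazard ratio is about 2/√153 = 0.162. The largest shift under no effect is ln(0.964/0.998) = −0.035, or 0.21 standard errors. The smallest is ln(0.995/0.998) = −0.003, or 0.02.

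**6. Without the covariate.** Nine covariates remain: 5 × 1 + 4 × 2 = 13 by the plan's count, and 153/13 = 11.8 events per variable.

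**The case against.** A reader might infer that adjuvant therapy is usually settled after randomisation. The article does not support that: it gives no adjuvant dates, and a window reaching 3 to 4 months leaves room for therapy to have been decided or begun. What stands is that the value is not guaranteed to be fixed.

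A reader might also infer that the trial's main result loses the protection of randomisation. It does not. The log-rank test, crude hazard ratio, survival medians and sample size make no use of this covariate.

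The relabelling route is possible but not described, and it is narrow. The section Recurrence diagnosis strongly advises pathological confirmation and asks for multidisciplinary consensus. The clinical route in Outcomes {12} needs growth on successive scans plus a raised CA 19-9 or PET activity, which a first scan cannot show alone, although biopsy remains open. The patient must also have accepted surveillance and not yet begun chemotherapy. The control arm is not free of scans either: Sample size {14} expects 5% to have routine imaging. When the label does not depend on the arm, both simulations show almost no shift, so late timing alone does little harm.

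Finally, coding rules may sit in the full protocol or analysis plan, and the word baseline could be read as status at baseline. That reading is fair, but the article names receipt as the variable, which is a stated choice and not merely an absent detail.

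**Conclusion.** The point holds in a limited form. The plan labels as baseline a treatment variable whose value may be settled after randomisation and which allocation could alter through the month-3 CT. That conflicts with its own reason for not adjusting for recurrence treatment. Under the assumed inputs the bias favours surveillance and runs from under 1% to about 4% of the hazard ratio. The upper end needs 90% of patients with open status and every eligible case relabelled. The size and direction rest on assumptions about early recurrence, late starters and relabelling that the article can neither confirm nor exclude. Only the additional adjusted hazard ratio is affected. The case for changing it is that adjustment for this variable is not needed to remove confounding in a randomised comparison, that a larger sample would not remove the bias, and that the correction is one line.

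**What to change.** Do one of the following before the final analysis:

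1. Drop adjuvant therapy from the adjusted Cox model. By the plan's count this leaves 13 terms and 11.8 events per variable, within its rule of about 10.
2. Replace it with adjuvant therapy intended (yes/no) in the postoperative plan documented before randomisation. The count stays at 15, or 153/15 = 10.2 events per variable.

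In either case, add that every covariate in this model is dated no later than randomisation. Defining the variable as adjuvant therapy started by the date of randomisation is a weaker option, because it partly measures how late a patient was randomised.

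The cost is one line of analysis wording and a slight loss of prognostic information in the adjusted model. The second option also needs the intended treatment to be recorded with a date. The log-rank test and the 306 patients are unchanged.
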